### 2.5. Sample Size

The primary outcome was the neonatal body temperature difference between KC prone position and KC lateral position. The sample size was calculated to achieve an 80% statistical power with an α of 0.05 to detect a 0.3 °C difference in the body temperature (DS 0.16) [5,13], and the non-inferiority margin was set at a 0.2 difference in body temperature [13]. In addition, we estimated a 10% loss to follow-up, so the sample size calculated is 35 participants in each group.

Additionally, the sample size was calculated to the secondary outcome; it was the difference in neonatal pain level between KC prone position and KC lateral position. With the same power an α to detect 0.83 points (DS 1), the non-inferiority margin was set at 1.53 points in PIPP-R, and we estimated a 10% loss, the sample size calculated is 29 participants in each group [5].

Given the scarce and heterogenous literature available on IVH [24], the populational behavior of this variable is unknown, with no references to calculate the sample size.

Therefore, the minimum estimated sample size to respond to the aims proposed is 35 subjects in each group.

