### 2.2. Design

The study is designed as a non-inferiority randomized parallel clinical trial.

The CONSORT guidelines for randomized controlled trials will be used. This protocol also adheres to the SPIRIT guidelines (Supplementary Materials: checklist SPIRIT).

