### 2.6. Randomization and Allocation

Participants will be recruited through non-probabilistic consecutive sampling.

Potentially eligible newborn patients will be identified in the research staff’s daily clinical practice or referred to them for eligibility assessment once they have been identified by clinicians who are not research staff.

Premature infants who meet all of the inclusion criteria and will be performing kangaroo care for the first time will be assigned to the experimental or control group on a simple 1:1 randomized basis, using a list of randomized numbers according to ID assignment from 1 to 70, using the random.org website.

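### The primary sample size assumes a 0.3 °C difference that lies outside its own 0.2 °C non-inferiority margin, so the stated 80% power does not follow from the stated inputs

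*Protocol article*

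**What the plan says.** Section 2.2 of the protocol article fixes the hypothesis: "The study is designed as a non-inferiority randomized parallel clinical trial". Section 2.5 then gives the basis for the primary outcome, neonatal body temperature:

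- Error rates: "The sample size was calculated to achieve an 80% statistical power with an α of 0.05". Sidedness is not given. Section 2.13 gives a 0.05 significance threshold, also without sidedness.
- Assumed difference and margin: 0.3 °C "difference in the body temperature (DS 0.16) [5,13], and the non-inferiority margin was set at a 0.2 difference in body temperature". The direction of the 0.3 °C is not given.
- Result: "we estimated a 10% loss to follow-up, so the sample size calculated is 35 participants in each group".

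Allocation is 1:1 (section 2.6). The same section sizes the secondary pain outcome: "With the same power an α to detect 0.83 points (DS 1), the non-inferiority margin was set at 1.53 points in PIPP-R". With 10% loss this gives 29 per group.

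**The concern.** A non-inferiority calculation takes the true difference that the planners expect and asks how often the confidence limit will stay inside the margin. The expected difference must therefore be smaller than the margin, or favour the new treatment. For temperature the order is reversed: 0.3 °C is larger than 0.2 °C. If lateral care really is 0.3 °C colder, it is inferior by more than the trial allows, and a sound trial should fail to show non-inferiority.

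Two things are at stake. The power claim for the primary outcome does not describe the trial. The text also leaves in doubt which figure is the margin, and the margin decides the conclusion. A confidence limit between 0.2 and 0.3 °C in lateral's disfavour would pass with one figure and fail with the other.

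**Working it through.** **Inputs (section 2.5).** SD 0.16; difference 0.3; margin 0.2; power 80%, so z = 0.842; α 0.05, so z = 1.645 if one-sided and 1.960 if each side takes 0.025; loss 10%. Allocation is 1:1.

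**Reproducing 35.** The formula is n per group = 2(z_α + z_power)² · SD² / (margin − deficit)², where the deficit is how much colder lateral is.

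- Distance: 0.2 − 0.3 = −0.1; squared, 0.01.
- n = 2 × (1.645 + 0.842)² × 0.0256 / 0.01 = 31.65.
- With loss: 31.65 × 1.1 = 34.8, or 31.65 / 0.9 = 35.2. Rounding up at both steps gives 32 / 0.9 = 35.6, so 36. The gap between 35 and 36 is rounding.

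The sign of the distance is lost in the squaring.

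**Checking the formula on pain.** Distance 1.53 − 0.83 = 0.70, SD 1: n = 2 × (2.487)² / 0.49 = 25.2, so 26; 26 / 0.9 = 28.9, so 29, as stated. The same formula and the same one-sided 0.05 apply, but here the assumed difference is inside the margin.

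**Other readings of the temperature inputs.**

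| Reading | Evaluable per group | With 10% loss |
|---|---|---|
| Margin 0.2, lateral 0.3 °C warmer (distance 0.5), one-sided 0.05 | 2 | 3 |
| Margin 0.2, true difference 0, one-sided 0.05 | 8 | 9 |
| Margin 0.2, true difference 0, one-sided 0.025 | 11 | 13 |
| Superiority at 0.3 °C, two-sided 0.05 | 5 | 6 |
| Distance 0.1, one-sided 0.025 | 41 | 46 |
| Distance 0.1, one-sided 0.05 | 32 | 36 (35 before the double rounding) |

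Only a distance of 0.1 °C with one-sided 0.05 returns the stated figure.

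**Power with the stated margin.** 35 less 10% is 31.5, so take 31 evaluable per arm. SE = 0.16 × √(2/31) = 0.0406. Power = Φ((0.2 − deficit)/SE − z_α).

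| True state of lateral | One-sided 0.05 | One-sided 0.025 |
|---|---|---|
| 0.3 °C colder | Φ(−2.46 − 1.645) ≈ 0.00002 (0.002%) | 0.000005 |
| 0.2 °C colder (at the margin) | 5% | 2.5% |
| 0.1 °C colder | Φ(2.46 − 1.645) ≈ 79% | 69% |
| No difference | 99.9% | 99.8% |
| 0.3 °C warmer | about 100% | about 100% |

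The noncentral t gives nearly the same values (78.5% and 67.8% at a 0.1 °C deficit).

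**The transposed reading.** With margin 0.3 and assumed deficit 0.2, the distance is 0.3 − 0.2 = 0.1, and the formula again gives 31.65 and about 35. Under that reading the calculation would be valid.

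**The case against.** The strongest reply is that the number of infants is not the problem. With margin 0.2 °C and SD 0.16, 35 per group gives power above 99% if the positions are equivalent. That stands. A reader might infer from the faulty calculation that the trial is too small, or that it cannot show non-inferiority; the documents do not support either. The near-zero power applies only if lateral is truly 0.3 °C colder. Section 2.5 does not say so, although the Introduction argues that side-lying could make thermoregulation harder because less skin is in contact. If the 0.3 °C favours lateral, the trial is far larger than needed, and 80% is still not its power.

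A second reply is that the two figures may simply have been swapped. This fits the arithmetic and the order used for pain, but section 2.5 names 0.2 as the margin and cites a source for it, so the documents cannot settle the matter. For the same reason it would be wrong to insert a 0.1 °C deficit as the planners' assumption: that value appears nowhere and is only back-solved from 35.

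Third, 0.3 with 0.2 would give 80% power for showing superiority by more than 0.2 °C. That is not the stated design.

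Finally, a condensed article may leave the sidedness of α and the direction of the margin to the full protocol. Their absence alone is no fault. They matter here because the stated figures conflict and 35 depends on them. No fuller document can place 0.3 inside 0.2.

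**Conclusion.** The concern holds as a fault in the stated justification. The printed difference and margin cannot both be right for a non-inferiority calculation, and 35 arises only by squaring a negative distance. At the stated margin and SD, with about 31 evaluable per arm and one-sided α 0.05, power is about 0.002% in one direction and about 100% in the other, against the stated 80%. These figures assume a normal approximation, the stated SD of 0.16 and the full 10% loss.

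The point does not establish that N is inadequate. Nor does it establish that 35 delivers 80% power under some other stated assumption: at a 0.1 °C deficit it gives about 79% with one-sided 0.05 and about 69% with one-sided 0.025. Which of the two temperature figures was the planning margin remains open.

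**What to change.** Before results are known, correct section 2.5 to state which figure is the margin and which is the assumed true difference, the direction of each, and whether α is one- or two-sided. Then restate the power that 35 per group delivers.

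- **If the margin is 0.2 °C:** remove the claim that the trial is sized to detect 0.3 °C. State that about 31 evaluable per arm with SD 0.16 gives about 79% power at a true deficit of 0.1 °C and above 99% at a true difference of 0 (one-sided α 0.05), or about 69% at a deficit of 0.1 °C with one-sided 0.025.
- **If 0.3 and 0.2 were transposed:** the 35 stands, but the margin used for the conclusion must be corrected and justified.

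The cost is one paragraph. N can stay at 35 provided the stated power is changed to match. Extra infants would be needed only if the sponsor wants 80% power at a distance of 0.1 °C with one-sided 0.025: 41 evaluable, or 46 per group with loss.

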### 2.13. Statistical Analysis

Normality associated with each quantitative variable will be analyzed using the test Kolmogorov–Smirnov test.

A descriptive analysis will be performed of the demographic and clinical characteristics of subjects in both treatment groups: quantitative variables will be described by mean or median and their dispersion measurements, standard deviation or interquartile range, respective, as appropriate. Qualitative variables will be described by absolute frequencies and percentages. The descriptive analysis will be accompanied by the 95% confidence interval.

Prior to testing hypotheses, we will check whether both groups are homogeneous in terms of the baseline characteristics, using Student’s *t*-test or Mann–Whitney U for quantitative variables or ANOVA or Kruskal–Wallis if the variable does not follow normal distribution, and if statistically significant differences are found, we will continue with post hoc Bonferroni contrasts or weighted comparisons with Mann–Whitney U. Chi-squared will be used for qualitative variables.

If the groups are heterogeneous, confounding factors will be defined to adapt the final analysis to the main variable.

The effectiveness of KC modified lateral position compared to the KC conventional prone position will be assessed, calculating axillary temperature variation (Student’s t-test or Mann–Whitney U), level of pain (Student’s *t*-test or Mann–Whitney U), and IVH development (Chi-squared) in both groups.

Intention to treat (NNT) and protocol analyses will be performed. Should the results be conflicting, protocol deviations and/or breaches will be analyzed.

Safety analysis in relation to adverse events will be calculated using Pearson’s Chi-squared test or Fisher’s exact test as appropriate.

An explanatory model with stepwise linear regression will be created based on a significance level of 0.1, and confounding variables and their level of importance will be determined.

The statistical significance level will be *p* < 0.05. Data will be analyzed with the Statistical Package for the Social Sciences-IBM SPSS^®^ program version 25.0 (IBM, Chicago, IL, USA).

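### The 80% power behind 35 per group rests on a 0.3 °C difference that lies outside the 0.2 °C non-inferiority margin, and on an undeclared one-sided 5% level

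*Protocol article*

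**What the plan says.** All references are to the protocol article.

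- Section 2.2: "The study is designed as a non-inferiority randomized parallel clinical trial".
- Section 2.5, level and power: "The sample size was calculated to achieve an 80% statistical power with an α of 0.05". No sidedness is given.
- Section 2.5, temperature: the aim is "to detect a 0.3 °C difference in the body temperature (DS 0.16"), and "the non-inferiority margin was set at a 0.2 difference in body temperature". The 0.3 °C carries no sign. After 10% loss, "so the sample size calculated is 35 participants in each group".
- Section 2.5, pain (PIPP-R): a 0.83-point difference, SD 1, margin 1.53 points and 10% loss; "the sample size calculated is 29 participants in each group". The section then adopts 35 per group for all aims.
- Section 2.13: one threshold of 0.05 for all tests ("The statistical significance level will be" p < 0.05), again without sidedness. Temperature and pain are compared by Student's t or Mann–Whitney U. The margin is not mentioned.
- Section 2.13, intervals: "The descriptive analysis will be accompanied by the 95% confidence interval". No interval is attached to the non-inferiority comparison.

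**The concern.** A non-inferiority sample size depends on the signed distance between the assumed true difference and the margin, and on the one-sided level of the test. Section 2.5 leaves the level open. For temperature it gives an assumed difference larger than the margin, so the expected result would lie either beyond the margin on the wrong side or far from it on the right side. Neither case produces 35 per group.

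Two things are at stake. The power quoted for the primary outcome may not describe the trial. And because one-sided 5% and one-sided 2.5% are both compatible with the text, the false-positive risk of a non-inferiority claim could be settled after the data are seen.

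**Working it through.** **Formula.** Evaluable n per group = 2(z_α + z_β)²·SD²/d², where d is the distance from the true difference to the margin, then divided by 0.9 for 10% loss. With z_β = 0.842, (z_α + z_β)² is 6.183 at one-sided 5% and 7.849 at one-sided 2.5%, the latter being the same as a two-sided 0.05 test or a 95% interval.

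**Reproducing the plan's figures.**

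| Outcome | d | One-sided 5% | One-sided 2.5% | Stated |
|---|---|---|---|---|
| Temperature, SD 0.16 | \|0.3 − 0.2\| = 0.1 | 31.65; /0.9 = 35.2 | 40.19; /0.9 = 44.7 | 35 |
| Pain, SD 1 | \|0.83 − 1.53\| = 0.70 | 25.23, up to 26; /0.9 = 28.9 | 32.04, up to 33; /0.9 = 36.7 | 29 |

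Rounding temperature up to 32 before inflation gives 35.6, so 35 matches within rounding. Using the difference alone, the margin alone or their sum for d gives 3 to 13 per group for temperature and 4 to 26 for pain, after inflation. None matches. Both stated sizes therefore point to one-sided 5% with the unsigned gap.

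**Giving the temperature gap a direction.** Take lateral minus prone, with non-inferiority meaning a true difference above −0.2 °C. With 32 evaluable per arm the standard error is 0.16 × √(2/32) = 0.04.

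- True difference −0.3: signed distance −0.3 − (−0.2) = −0.1. The lateral position is inferior. The chance of claiming non-inferiority at one-sided 5% is Φ(−0.1/0.04 − 1.645) = Φ(−4.145), below 0.01%.
- True difference +0.3: distance 0.5, and 2 × 6.183 × 0.0256/0.25 = 1.3 per group would suffice.
- A distance of +0.1 requires a true difference of −0.1 °C, which section 2.5 does not state.

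For pain, 0.83 lies inside the 1.53 margin, so a deficit of 0.83 leaves a valid distance of 0.70. The directional defect concerns temperature only.

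**Effect of the level, keeping d as the plan used it.** Power = Φ(d/(SD√(2/n)) − z_α). The evaluable number is 35 × 0.9 = 31.5, so n = 31 and 32 are shown.

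| Outcome | n per arm | One-sided 5% | One-sided 2.5% |
|---|---|---|---|
| Temperature, d 0.1 | 31 | 79.3% | 69.2% |
| Temperature, d 0.1 | 32 | 80.4% | 70.5% |
| Pain, d 0.70 | 31 | 86.7% | 78.7% |
| Pain, d 0.70 | 32 | 87.6% | 80.0% |
| Pain, d 0.70, its own 29 per group | 26 | 81.0% | 71.4% |

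With the noncentral t, temperature at one-sided 2.5% is 67.8% (n = 31) and 69.2% (n = 32).

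**What 35 per group can support.** At zero true difference d = 0.2, and with n = 31 the standard error is 0.0406. Power at one-sided 2.5% is Φ(0.2/0.0406 − 1.960), about 99.8%. The largest lateral deficit that keeps 80% power at n = 32 is 0.2 − 0.04 × (z_α + z_β): 0.2 − 0.04 × 2.802 = 0.088 °C at one-sided 2.5%, and 0.2 − 0.04 × 2.486 = 0.10 °C at one-sided 5%.

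**The case against.** The strongest reply is that the document does not contradict itself on the level. Alpha 0.05 in section 2.5 and p < 0.05 in section 2.13 are both silent on sidedness, a one-sided 5% test satisfies both, and 35 and 29 then reproduce. That stands. A reader might infer that the plan's own test and interval cut the power from 80% to 70%. The article does not support this, because it names no two-sided test and ties the 95% interval to the descriptive analysis, not to the non-inferiority decision. Two-sided use is plausible where ordinary t, Mann–Whitney and chi-squared tests share one threshold, but it is an assumption.

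A reader might also infer the same shortfall for pain. The 71% applies only to 29 per group; the trial plans 35, and pain then has about 79% even at one-sided 2.5%.

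It can be said, too, that sidedness may be left to an analysis plan that is not shown. That is fair for sidedness alone. It does not cover the temperature calculation, which is published with a difference and a margin that do not fit together.

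Finally, zero true difference is not the document's assumption; the Introduction expects that reduced skin contact in the side-lying position could make thermoregulation harder. The 99% figure is therefore an illustration, not a substitute calculation.

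**Conclusion.** The point holds in two parts of different strength.

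1. Without any assumption about sidedness, the 80% power for temperature is not a power for the stated non-inferiority hypothesis. It comes from an unsigned 0.1 °C gap that neither direction of a 0.3 °C difference produces.
2. Conditionally, if non-inferiority is judged two-sided at 0.05 or by a 95% interval, power on the plan's own inputs is about 70% for temperature (31 to 32 evaluable per arm) and about 79% for pain. Reaching 80% for temperature would then take about 45 to 46 per group.

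The figures in part 2 inherit the disputed 0.1 °C distance. They show how much the undeclared level matters and are not an estimate of the trial's true power. None of this shows that 35 per group is too few: depending on the true difference, the same 35 gives anything from almost no chance of success to over 99%. All figures assume SD 0.16 (temperature) or 1 (pain), 10% loss and a comparison of two means.

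**What to change.** - **Section 2.5, temperature.** State the assumed true difference (lateral minus prone) with its sign, reconcile it with the 0.2 °C margin, and restate the power of 35 per group under it. For illustration, zero true difference with SD 0.16 gives over 99% at one-sided 2.5%.
- **Sections 2.5 and 2.13, level.** State one level and the matching interval whose limit is compared with the margin: one-sided 2.5% with the 95% interval, or one-sided 5% with the 90% interval. Quote the power for temperature and pain at that level.
- **Section 2.5, pain.** Give the power at the 35 per group actually planned as well as the stand-alone 29.

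The cost is a few sentences and restated figures, settled before the data are analysed. The change adds no infants. If the restated temperature power falls below 80%, that should be reported as it is.

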### 2.6. Randomization and Allocation

Participants will be recruited through non-probabilistic consecutive sampling.

Potentially eligible newborn patients will be identified in the research staff’s daily clinical practice or referred to them for eligibility assessment once they have been identified by clinicians who are not research staff.

Premature infants who meet all of the inclusion criteria and will be performing kangaroo care for the first time will be assigned to the experimental or control group on a simple 1:1 randomized basis, using a list of randomized numbers according to ID assignment from 1 to 70, using the random.org website.

### 2.7. Blinding

Both clinicians/caregivers and research nurses will be informed of the group to which each participant is assigned due to their involvement in facilitating the care intervention for each group. However, non-caregiver researchers and those responsible for processing and analyzing the data will be blinded to assignment.

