### 2.11. Data Collection Methods

See Table 1: Participant timeline.

The following dependent variables will be obtained:Premature infant axillary temperature measured continuously with the temperature probe fixed (AirLife^TM^ Infant Skin temperature probe (Vyaire Medical Inc, Chicago, IL, USA), Giraffe^®^ incubator (GE Healthcare, Chicago, IL, USA) on the axillary infant with adhesive tape (protect the infant skin with hydrocolloid tape before).

The axillary temperature will also be taken with a Braun^®^ PRT2000 (Braun GmbH, Kronberg, Germany) thermometer.

Neonatal pain level assessed by Premature Infant Pain Profiled Revised. PIPP-R is a multidimensional scale (it includes physiological, behavioral, and facial expression signs for the pain assessment) developed by Stevens B [29], is valid for assessing pain in full-term and preterm neonates during painful procedures. Scores range from 0 to 21; score minor to 7 is interpreted as no pain or minor pain. Studies validating the scale show a high correlation between PIPP and PIPP-R is not painful (R2 = 0.91, *p* < 0.0001) and painful (R2 = 0.98, *p* < 0.0001) procedures. Average applicability scores are 3.5–3.7 (average of 4 out of 5) [30].

●Intraventricular hemorrhage (IVH) assessed by cranial ultrasonography using Siemens AcusonX300 ^®^ ultrasound system (Siemens AG, Berlin, Germany):
○IVH presence: yes or no.○Grade [31]
-Grade 1: hemorrhage located in the subependymal germinal matrix.-Grade 2: intraventricular blood content occupies less than 50% of the intraventricular area.-Grade 3: blood occupies >50% and distends ventricle.-Grade 4: significant overdistension of lateral ventricles and the entire ventricular system in general.○Location: right, left, or bilateral.○Date of cranial ultrasonography.

Transfontanelar ultrasound will be performed at two different times, the first before the first KC session by a specialist in neonatology with specific training in neonatal ultrasound, under early IVH detection screening. The head US done before the first KC session is used as a control US to identify the presence of congenital HIV or bleeding on the first hours of life. This way, we can determine it is not associated with the kangaroo position in prone.

The second ultrasound at 48 h of life (according to the study unit protocol) by a specialist in radiodiagnosis.

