### 2.15. Monitoring

An interim analysis is performed on the primary endpoint when 20% of patients have been randomized. The idea is to be able to identify an increase in HIV incidence in the control group, such as other potential hazard events in all participants. In that case, the study would come to a halt. The main investigator will have unblinded access to data and will discuss the results of the interim analysis with the research team.

The trial will not be stopped in case of futility related to the outcome variables because kangaroo care is the current intervention in the neonatal units due to clinically proven benefits, so futility is not sustainable.

The main investigator has the ultimate authority to stop or modify the trial and to ensure the protocol’s continued. He will follow up with all participants, and he will check all kangaroo care sessions are completed as it is referred to in the protocol. If that is not the case, the session will be discarded.

Changes on the protocol will be notified to all team members immediately and keeping all documentation standardized. All updated versions will be available in a digital form, and team members will be noticed during practical and theoretical lectures.

Safety and complications were monitored by identifying kangaroo potential adverse events noted down in the Data Collection Logbook (DCL), such as hypothermia, continuous hemodynamic instability during kangaroo care, or accidental displacement of any therapeutic device. Those events will be collected and analyzed in the first 24 h by the investigator in charge of the session, notifying the main investigator. The main investigator will record this adverse event on the study database, taking the actions required according to the severity and impact.

A committee in charge of data monitoring has not been created, the tracking is carried out by the research team. Non-audits have been scheduled.

Preliminary analyses every 20 new participants will be done to discard a rising HIV incidence in the control group, which would mean the study would come to a standstill.

Established withdrawal criteria are hypothermia or a Kangaroo care session less than 60 min.

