The possible limitations of the study are as follows: (a) in terms of the study population, due to the immaturity of the premature infants, the sample size may be reached in a broad period of time caused as possible hemodynamic instability may not allow kangaroo care the first days of life; (b) regarding intervention, the first kangaroo care session may be delayed until approximately 20 h of life due to the numerous formalities required of the father, and as the mother is normally not available to act as kangaroo due to health issues as she is not admitted in the same room as the baby; (c) related to biased information as the data collection notebook is not fully filled in due to healthcare team workload, always guaranteeing the collection of dependent variables; (d) ultrasound sensitivity in early intraventricular hemorrhage detection; (e) the relatively small sample size for the IVH outcome. The sample size for this secondary outcome was not calculated due to the heterogenous literature available about IVH in relation to the risk that would be caused by the prone position compared with the other positions; and finally, (f) pain is measured on the validated PIPP-R scale but not validated in Spanish; there is currently no validated scale in Spanish for assessing neonatal pain. In addition, with regard to the assessment of pain, it will not be possible to blind the observers or to carry out the measurement of pain by two professionals independently.

These restrictions will be taken into account during data analysis, analyzing missing values, and, if necessary, completing simple imputation of these values.

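### The blinding section does not mask the specialists who read the cranial ultrasounds, so IVH, a secondary outcome and a named reason to halt, can be read with the kangaroo position known

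*Protocol article*

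**What the plan says.** Section 2.7 (Blinding) sorts the staff into two groups. On one side, "Both clinicians/caregivers and research nurses will be informed of the group to which each participant is assigned", and the reason given is "due to their involvement in facilitating the care intervention for each group". On the other, "non-caregiver researchers and those responsible for processing and analyzing the data will be blinded to assignment".

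Section 2.11 (Data Collection Methods) describes two cranial ultrasounds. The baseline scan is "the first before the first KC session by a specialist in neonatology with specific training in neonatal ultrasound". The later one is described as follows: "The second ultrasound at 48 h of life (according to the study unit protocol) by a specialist in radiodiagnosis". Table 1 lists the person responsible only as a physician. Neither place says whether the reader knows the kangaroo care (KC) position.

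Section 2.15 (Monitoring) plans an interim look at 20% of randomization and further looks every 20 new participants, in order to detect a rise of IVH in the control (prone) arm, "which would mean the study would come to a standstill". The abbreviation is printed there as HIV; I read it as IVH. The same section also names other hazard events as a ground for halting, gives the main investigator unblinded access, and states that there is no data monitoring committee.

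**The concern.** The outcome reading sits outside the group that section 2.7 protects. Both readers are clinicians. Neither processes or analyzes data, and neither is named as a blinded researcher. The reason given for informing clinicians, that they help deliver the position, does not apply to someone reading a scan.

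The position is also easy to find. Under section 2.8, data from all KC sessions go into the medical record. Under section 2.11, position is recorded at each session and the IVH data are taken from the patient's medical history.

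The Introduction sets out a mechanism by which the turned head in prone could raise IVH risk. A reader who knows the position and the hypothesis could resolve a doubtful image differently in the two arms. At stake are a stated secondary aim (section 2.1, aim a) and a comparison that can halt the trial. The primary temperature outcome is not affected.

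**Working it through.** The plan states no figure on this point, so there is nothing to reproduce. The check has two parts.

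**Part 1. Who is covered by the blinding statement**

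| Role | Source | Informed of arm? | Named as blinded? |
|---|---|---|---|
| Clinicians/caregivers who facilitate KC, research nurses | 2.7 | Yes | No |
| Non-caregiver researchers, data processors and analysts | 2.7 | No | Yes |
| Neonatologist, baseline scan | 2.11 | Not stated individually; a clinician | No |
| Radiodiagnosis specialist, 48 h scan | 2.11 | Not stated individually; a clinician | No |

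The baseline scan precedes the first KC session, so no position has yet been used. Table 1 places the scan and the allocation in the same column before the first session and does not order them. The exposure is therefore mainly at the 48 h scan.

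**Part 2. How much a few readings can move the comparison**

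Inputs from the protocol article: 35 infants per arm (2.5), an IVH rate of 20–38% (Introduction), a first look at 20% of 70 (2.12, 2.15), and a chi-squared test at p < 0.05 (2.13). Assumptions, with no source in the document: the number or rate of over-called prone scans, equal true rates in the two arms, and an even split at the first look.

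- Expected events per arm: 35 × 0.20 = 7; 35 × 0.38 = 13.3, taken as 13.
- Two over-called prone scans at full size: 2/35 = 5.7 percentage points. Relative risk = (7 + 2)/7 = 9/7 = 1.29, or (13 + 2)/13 = 15/13 = 1.15.
- In terms of a rate, these two scans are 2/(35 − 7) = 7.1% or 2/(35 − 13) = 9.1% of prone infants without IVH.
- First look: 0.20 × 70 = 14 infants, about 7 per arm. One over-called prone scan adds 1/7 = 14 percentage points.

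To show a range, let a fraction f of prone infants without IVH be over-called. The observed prone rate is p′ = p + (1 − p)f, the lateral rate stays at p, and the probabilities are exact binomial sums.

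| True rate p | Assumed f | p′ | P(more IVH in prone), 7 per arm | P(chi-squared significant against prone), 35 per arm |
|---|---|---|---|---|
| 0.20 | 0 | 0.200 | 36.6% | 2.4% |
| 0.20 | 0.05 | 0.240 | 44.2% | 5.7% |
| 0.20 | 0.10 | 0.280 | 51.6% | 11.4% |
| 0.20 | 0.20 | 0.360 | 65.0% | 31.8% |
| 0.38 | 0 | 0.380 | 39.2% | 2.5% |
| 0.38 | 0.05 | 0.411 | 44.0% | 4.4% |
| 0.38 | 0.10 | 0.442 | 48.8% | 7.2% |
| 0.38 | 0.20 | 0.504 | 58.3% | 16.7% |

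The article does not put a number on the rise that would halt the trial, so the 7-per-arm column is the chance of seeing any excess in prone, not a chance of halting. The 20–38% rate covers all IVH, including bleeds that the baseline scan is meant to separate out. If only new bleeds are counted, there are fewer true events: two over-calls still add 5.7 points when all 35 infants remain in the denominator, but the relative risk moves further.

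**The case against.** The strongest reply is that the article never says the radiodiagnosis specialist is told the arm. Clinicians are informed because they facilitate the intervention, Table 1 gives both interventions to the neonatal nurse, and the 48 h scan follows the unit's own protocol. The masking procedure might also be set out in the full protocol. The first part stands: a reader might infer that IVH is read unblinded by design, and the text does not support that. The second part carries less weight, because the article has a dedicated section that lists who is informed and who is blinded, and this outcome's readers are absent from the blinded list.

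Other stronger readings are tempting and also fail:

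- A reader might infer that IVH in prone is the only stop rule. Section 2.15 also names other hazard events in all participants.
- A reader might take the Discussion to say that blinding is impossible only for pain. It says that pain observers cannot be blinded and is silent on ultrasound.
- A reader might use the stated limitation "ultrasound sensitivity in early intraventricular hemorrhage detection" as evidence of over-calling. Limited sensitivity means missed bleeds; the article describes no problem of false positives.
- A reader might assume that the scan readers expect harm in prone. The Introduction gives a mechanism but calls the evidence scarce and of low quality, and nothing shows what the readers believe.
- A reader might infer that the baseline scan is read after allocation. Table 1 leaves the order open. An over-called baseline scan in prone would also push the comparison the other way, so the net direction of any bias is not determined.

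Finally, a request form without the position cannot guarantee masking when session data are in the medical record. That is a fair limit on the fix.

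**Conclusion.** The concern holds as a gap in protection. The blinding section leaves the reading of IVH unmasked by any stated measure, although masking is feasible and the outcome is both a secondary aim and one named ground for halting. It does not show that the reader is told the arm or that bias will occur.

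The sizes are illustrations that rest on assumed over-calls in prone only: 5.7 points for two scans among 35 (relative risk 1.29 or 1.15), and 14 points for one scan among about 7 at the first look. With equal true rates, the chance of a significant result against prone goes from about 2.5% to 7–11% at an assumed 10% over-call rate and 17–32% at 20%. The change should be made because it is cheap and IVH informs the decision to halt.

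**What to change.** 1. In sections 2.7 and 2.11, state that the existing radiodiagnosis specialist reads the 48 h scan without being told the KC position. The request carries no position, and IVH presence, grade and side are recorded before any discussion with the care team or review of the KC session records. The result is then released for care as usual.
2. In Table 1, state that the baseline scan result is recorded before the allocation is opened.
3. Where masking fails, record that it failed, and list unmasked IVH reading among the limitations in the Discussion.

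The cost is a few sentences of protocol text, a request form without position and one extra data item. No additional reader or scan is needed. The small downside is that masking may be imperfect, because the position can be found in the medical record.
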